## 8. STRATEGIES AND TREATMENTS

### Strategies

#### Arm 1: Facility-based testing intervention

Community Health Workers (CHWs) will provide information on the possibility to be tested in health centers for HCV infection. Information will be provided using information sheet and a dedicated leaflet in the selected households. If the participant agrees to participate, she/he will receive a voucher to go to referral health center for testing. In health center, after signature of

consent form, HCV testing will be done using HCV RDT on a finger stick capillary whole blood. Results will be available in 15 minutes. In case of positive HCV RDT, an immediate blood sample collection (5 mL of whole blood on EDTA) will be done in health center and sent to Provincial hospital laboratory to collect plasma. Plasma will be sent to UHS to perform HCV RNA. Results will be sent back to the health center and nurses will be in charge to give result to the participant and to refer to care in case of active infection (systematic appointment + phone call if the participant doesn't come).

### Arm 2: Community-based testing intervention

After a dedicated training, CHWs will do the HCV RDT on a finger stick capillary whole blood directly in the household of participant. Information will be provided by the CHW using information sheet and a dedicated leaflet. If the participant agrees to participate, the signed consent form will be collected at this step before any RDT collection. In case of structural or societal barriers for household testing, it will be possible to provide testing in a specific location in the village. The visits will be planned with the head of village and he will be in charge to inform the population. In case of absence of participant during the first visit, a second visit will be scheduled. In absence of participant during the second visit, no additional visit will be planned.

In case of positive HCV RDT, 5 blood spots will be collected immediately on DBS, put in a specific plastic bag with the ID number and sent to UHS (Rodolphe Merieux laboratory) for HCV RNA extraction and amplification. Results will be sent back to the referral health center of each village and nurses will be in charge to give result to the participant and to refer to care in case of active infection (systematic appointment + phone call if the participant doesn't come).

### Patients with a known HCV positive status

Patients with a known HCV positive status will be tested by RDT to confirm HCV infection and will be followed according to the procedure described above. Patients with a prior history of HCV treatment could not be enrolled in the study.

### Common management in the provincial hospital for positive HCV RNA patients

For negative HCV RNA, a specific counseling will be done.

For positive HCV RNA, a consultation in the Provincial Hospital will be planned. In the absence of consultation within 4 weeks, SMS reminder will be sent to participant. A correlation table will be available in the provincial hospital to confirm the identification of the participant. Trained general practitioners will do the consultation with the possible support of hepatologist by phone. The baseline assessment will include questionnaires (risk behaviours and socio-economic status), clinical exam, blood sampling and liver ultrasound.

Symptomatic cirrhotic patients will be defined as patients with at least one of these signs: ascites, collateral circulation of the abdominal wall around the umbilicus, encephalopathy, jaundice, HCC. These patients will be referred to a National Hospital in Phnom Penh to a hepatology unit.

For the others patients, DAA treatment will be proposed, after checking the result of creatininemia and the possible drug-drug interactions.

### **Treatments used in the study**

None of the drugs used in the study is experimental.

Combination of daily sofosbuvir (400 mg) and daily daclatasvir (60 mg) will be provided to patients for a total duration of 12 weeks. DAA treatment will be introduced at the first consultation in the provincial hospital with a monthly follow-up. WHO pre-qualified Generic drugs (Hetero labs limited) will be used. The dose will be Sofosbuvir 400 mg one tablet per day and Daclatasvir 60 mg one tablet per day.

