#### **Patients with HIV co-infection**

- If HIV infection is known, ART-treated with a HIV RNA VL < 1000 copies/mL, patient could be treated with DAA considering the possible drug-drug interaction between ART and DAA. A reduced DCV dose (30 mg daily) will be recommended for patients receiving ritonavir-boosted atazanavir or other potent inhibitors of cytochrome P450 3A4 (CYP3A4) or P-glycoprotein, and a dose increase (90 mg) recommended with efavirenz or other moderate inducers of CYP3A4.

- If HIV infection is just diagnosed or not virologically controlled, patient will be addressed to the referral ART site to receive specific care before any intervention for HCV infection.

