#### **Treatments used**

Sofosbuvir: 400 mg once daily

Daclatasvir: 60 mg once daily

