#### **Treatments that could not be used or use with precaution because of potential drug-drug interactions**

Refer to the respective SmPC daclatasvir and sofosbuvir in Appendix 7 and 8 for drug interaction information in medicinal products and Appendix 9 for the main drug-drug interactions.

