## **21.APPENDIX**

**Appendix 1: Information sheet screening phase**

**Appendix 2: Consent form screening phase**

**Appendix 3: Information sheet treatment phase**

**Appendix 4: consent form treatment phase**

**Appendix 5: composition of the SAB**

**Appendix 6: composition of the DSMB**

**Appendix 7: Interview guides for acceptability study**

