**Appendix 8: Recruitment material for the acceptability study (Information sheet and consent form of acceptability study)**

## Appendix 5 : composition of the SAB

[figure not shown]

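### Daclatasvir is 60 mg without exception in two places and 30 or 90 mg by co-medication only under the HIV heading; the scope for patients without HIV is unstated, and the interaction section cites appendices that do not hold the information

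*Protocol*

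**What the plan says.** All dose statements are in Protocol Section 8.

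- **Treatments used in the study.** The regimen sentence reads "Combination of daily sofosbuvir (400 mg) and daily daclatasvir (60 mg) will be provided to patients for a total duration of 12 weeks". The same paragraph then says "The dose will be Sofosbuvir 400 mg one tablet per day and Daclatasvir 60 mg one tablet per day". No exception or cross-reference is given.
- **Patients with HIV co-infection.** In the bullet for known, ART-treated and virologically controlled HIV: "A reduced DCV dose (30 mg daily) will be recommended for patients receiving ritonavir-boosted atazanavir or other potent inhibitors of cytochrome P450 3A4", extended to P-glycoprotein inhibitors. The same sentence recommends 90 mg with efavirenz or any further moderate CYP3A4 inducer.
- **Treatments used.** "Daclatasvir: 60 mg once daily", again without exception.
- **The interaction subsection that follows.** "Refer to the respective SmPC daclatasvir and sofosbuvir in Appendix 7 and 8 for drug interaction information", and Appendix 9 for the main interactions.

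Section 21 lists "Appendix 7: Interview guides for acceptability study" and "Appendix 8: Recruitment material for the acceptability study". Its list stops there.

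The Study Summary (treatment phase) and Section 8, Common management in the provincial hospital, both require possible drug-drug interactions to be checked before DAA treatment is proposed.

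**The concern.** The adjustment is triggered by a class of drug, and its wording reaches beyond antiretrovirals. Yet it stands only under a heading for patients with HIV. The two 60 mg statements cover every treated patient and do not mention it. A prescriber whose HIV-negative patient takes a drug of one of those classes therefore finds two statements and no rule for choosing between them.

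The subsection that should decide the matter sends the reader to the wrong appendices. The check it supports is compulsory. It falls to trained general practitioners, for whom hepatologist support by phone is possible, and treatment starts at the first hospital consultation.

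At stake are daclatasvir exposure and safety in those patients. A lesser issue is clarity about which regimen was given when SVR12 and safety of the 12-week dual therapy are reported.

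**Working it through.** There is no plan figure to reproduce. The check sets the statements side by side.

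**1. Which dose statement reaches which patient?**

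| Patient | Treatments used in the study; Treatments used | Patients with HIV co-infection | Result on the text |
|---|---|---|---|
| No interacting drug | 60 mg | no adjustment | 60 mg, clear |
| Controlled HIV on ART, potent CYP3A4 or P-gp inhibitor | 60 mg | 30 mg | specific exception; cross-reference missing |
| Controlled HIV on ART, moderate CYP3A4 inducer | 60 mg | 90 mg | specific exception; cross-reference missing |
| No HIV, drug of either class | 60 mg | class named, heading does not apply | not settled |

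The last row is the gap. Taken by its heading, the HIV subsection leaves such a patient at 60 mg. Taken by its drug-class wording, it points to 30 or 90 mg. The protocol does not choose.

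**2. How far apart are the statements?** 60 / 30 = 2 for inhibitors and 90 / 60 = 1.5 for inducers.

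**3. Does the interaction subsection resolve it?**

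| Cited | Said to hold | Section 21 lists |
|---|---|---|
| Appendices 7 and 8 | the two SmPCs | 7: interview guides; 8: recruitment material |
| Appendix 9 | main interactions | not listed |

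Section 15.4 uses Appendices 7 and 8 in the same way as Section 21. All three references therefore fail. This rests on the appendix titles, not on their contents.

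**4. Does another place resolve it?** The Study Summary and Common management require the interaction check but attach no dose consequence to it. Section 11.2.2 refers to the SmPCs for concomitant drugs, without an appendix number. It identifies the source but does not say whether the HIV adjustment extends to other patients.

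**The case against.** The strongest reply is that this is ordinary drafting: a general dose, then a specific exception under its own heading. For HIV co-infected patients that stands. A reader might infer that the protocol contradicts itself for them, but only a cross-reference is missing.

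For everyone else, the reply is that safeguards exist. The interaction check applies to all patients, the interaction subsection is not confined to HIV, and the SmPCs are named there, in Section 11.1.4 and in Section 11.2.2. Contraindications bar treatment, and the Decision Support Committee advises on DAA management. This stands in part. A careful prescriber could obtain the SmPC despite the wrong number, so it would be too strong to say that the check cannot be done. Nor do the documents show that different doses would in fact be given: that depends on SmPC content which is not in the protocol. They show only that the text permits it.

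A reader might also infer that 30 or 90 mg cannot be supplied because the only tablet described is 60 mg. The protocol does not say that 60 mg is the sole strength procured, and Section 8, Supply, leaves procurement to the data management centre.

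Finally, the primary endpoint is testing uptake, and SVR12 is reported overall rather than compared between arms. The point therefore does not touch the main comparison. That is correct and limits its weight.

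**Conclusion.** The point holds as an operational dosing ambiguity combined with a wrong pointer for a mandatory safety check. Two subsections state 60 mg without exception, and one states 30 or 90 mg by drug class under a heading that excludes most patients. Nothing in the protocol says which applies to a patient without HIV on a drug of those classes. None of the three cited appendices is listed as holding interaction information.

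The conflicting doses differ by a factor of 2 or 1.5. How many patients this concerns cannot be derived. A reader might start from the plan's 300 antibody-positive persons and the 70% viraemic fraction in Section 3 (300 × 0.70 = 210). That fraction comes from an HIV treatment cohort, however, and the protocol gives no figure for the share of HIV-negative patients taking an interacting drug. The conclusion does not depend on a count. It assumes only that some treated patients without HIV may take such a drug. It expresses no view on which dose is right.

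**What to change.** The sponsor should:

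1. Reconcile the four subsections of Section 8 (Treatments used in the study, Patients with HIV co-infection, Treatments used, and the interaction subsection) so that each refers to the same dosing rule. Which rule stands is the sponsor's decision.
2. State explicitly whether the adjustment under the HIV heading applies to patients without HIV who take a drug of the same class.
3. Correct the interaction subsection and the Section 21 list so that the two SmPCs and the interaction table are listed, and attached, under numbers that exist.

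An optional addition is to record the prescribed daclatasvir dose in the CRF. The dispensing record in Section 8, Accountability, names the drug, batch and expiry date but not the dose.

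The cost is a protocol wording change, attachment of three reference documents and, if wanted, one CRF field. No extra patients, visits or samples are needed.

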#### Supply

All investigational medicinal products will be sourced from Good Manufacturing Practices (GMP) certified manufacturers. The Monitoring and Data Management Center (MDMC) will centralize the procurement of these products and ensure access to these drugs to Provincial hospitals for the total duration of the study.

#### Packaging and labelling of IMP

In this study, investigational medicinal products will be prepared, packed and labelled in accordance with GMP (international conference of harmonization (ICH) guide for active pharmaceutical ingredients Q7,2000, <http://www.gmp-compliance.org/guidemgr/files/3-1-18.PDF>). A specific study label will be added to each drug bottle in compliance with the GMP and Cambodian laws and regulations. The label templates will be validated by the MDMC and the sponsor.

#### Handling and storage

The IMP's will be delivered by supplier to the University of Health Sciences at the beginning of the study and eventually during the study. The MDMC will store the IMP's at room temperature in a locked environment. The responsible pharmacist or investigator will maintain a temperature control log and medication inventory. Details on handling, shipment and storage of study drugs will be specified in a separate document (study specific standard operating procedures).

#### Responsibilities

In compliance with ICH Good Clinical Practices (GCP), the responsibility for the IMPs at the study site lies with the investigator and pharmacist and includes the following:

- Receipt of the study medication;
- Documentation of deliveries;
- Adequate management, storage and destruction of study medications;
- Keeping of records including dates, quantities and the batch numbers / expiry date assigned to the investigational medication and ID study subjects;
- Documentation including the dispensation of the study medications to subjects as specified by the protocol;
- Reconciliation of all investigational medications.

The following guidelines apply:

- The investigator agrees not to supply any medication to any person except to the patients included in the study;
- The pharmacist agrees to keep the medications in a locked, secure, storage facility, only accessible to authorized staff;
- A study medications inventory is maintained, including materials received and dispensed to patients;
- During the study, the pharmacist agrees to conduct a drug supply inventory and to record this on a Drug Accountability form.

The supply and handling of other drugs than IMPs provided to participants for their care will be performed according to the usual procedures of the study sites.

#### Accountability

Every time medication is dispensed, the pharmacist will record the study subject identification code, the name of the drug, the batch number, the expiry date and the accountability on the Drug Accountability form. Patients will be asked to bring back bottles of used or left-over drugs. The Drug Accountability form will be checked by the CRA during on site monitoring.

Once accountability has been checked by the study monitor, during the study and at the end of the study, any remaining drugs brought back by the patient will be destroyed by the pharmacy of the trial site, according to each country's regulations.

#### Treatment follow-up

Monthly consultation and treatment delivery will be applied. All adverse events will be assessed by the investigator and documented regardless of the possible causality with the concomitant treatments. Adherence will be evaluated every month using questionnaire and visual analog scale. Biological follow-up during the treatment is reported in table 1.

Treatment will not be initiated in the following situation:

- Indication to palliative care
- Hepatocellular carcinoma (HCC) diffuse with infiltration
- Hepato-renal syndrome type 1
- Severe renal insufficiency defined as a creatinine clearance < 30 ml/mn
- Active pregnancy
- Breastfeeding
- Contraindication for treatment with sofosbuvir or daclatasvir
- Hypersensitivity to the active substance or to any excipients
- Any condition which might, in the investigator's opinion, compromise the safety of the patient including very severe clinical condition

#### **Patients with cirrhosis**

Asymptomatic cirrhotic patients will be treated as the other patients and followed in the Provincial Hospital with sofosbuvir/daclatasvir combination for 12 weeks.

Symptomatic cirrhotic patients will be referred to National Hospital and treatment will be discussed case by case. Additional exams will be funded by the study. In case of difficult situation, a Decision Support Committee will help the physicians to take a decision.

#### **Patients with HIV co-infection**

- If HIV infection is known, ART-treated with a HIV RNA VL < 1000 copies/mL, patient could be treated with DAA considering the possible drug-drug interaction between ART and DAA. A reduced DCV dose (30 mg daily) will be recommended for patients receiving ritonavir-boosted atazanavir or other potent inhibitors of cytochrome P450 3A4 (CYP3A4) or P-glycoprotein, and a dose increase (90 mg) recommended with efavirenz or other moderate inducers of CYP3A4.

- If HIV infection is just diagnosed or not virologically controlled, patient will be addressed to the referral ART site to receive specific care before any intervention for HCV infection.

#### **Patients with HBV co-infection**

All patients with HCV active infection will be tested for HBsAg at inclusion. If HBsAg is positive, a treatment by tenofovir will be initiated from inclusion until 12 weeks after discontinuation of HCV treatment.

In case of sudden rising of ALT level during follow-up of HCV treatment, HBV DNA will be performed to eliminate reactivation of occult HBV infection and a treatment by tenofovir could be initiated in case of positive result.

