## 9. STUDY IMPLEMENTATION

### Study schedule

|                                | Testing phase  | Therapeutic phase for positive HCV RNA | W4 | W8 | W12 | W24            | W28 |
|--------------------------------|----------------|----------------------------------------|----|----|-----|----------------|-----|
| Consent form                   | X              | X                                      |    |    |     |                |     |
| Eligibility criteria           | X              | x                                      |    |    |     |                |     |
| Consultation and clinical exam |                | x                                      | x  | x  | x   | x              | x   |
| HIV RDT                        |                | x                                      |    |    |     |                |     |
| HBs Ag RDT                     |                | x                                      |    |    |     |                |     |
| HCV Ab RDT                     | X              |                                        |    |    |     |                |     |
| HCV RNA plasma                 | x  |                                        |    |    |     | x              |     |
| HCV RNA DBS                    | x  |                                        |    |    |     |                |     |
| AST / ALT                      |                | x                                      | x  | x  | x   | x              |     |
| Creatinine                     |                | x                                      | x  | x  | x   |                |     |
| CBC                            |                | x                                      | x  |    |     | x              |     |
| Pregnancy test     |                | x                                      | x  | x  |     |                |     |
| PT                             |                | x                                      |    |    |     | x  |     |
| Bilirubin                      |                | x                                      |    |    |     | x  |     |
| Albumin                        |                | x                                      |    |    |     | x  |     |
| Fasting glycemia               |                | x                                      |    |    |     |                |     |

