### **Visit W28**

This visit will be the last visit of the study. In case of SVR12, patients will be informed of the cure. Recommendations to continue liver ultrasound follow-up every 6 months will be given for cirrhotic patients.

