### **Permanent study treatment discontinuation**

Reasons for permanent discontinuation of study treatment include:

- Willingness of the patient;
- Any medical event requiring discontinuation of the study treatment (drug-intolerance or occurrence of Serious Adverse Events (SAE), occurrence or worsening of a concomitant illness);
- Need for the patient to be treated with a non-authorized concomitant medication;
- Death of the patient;
- Non-adherence to the study treatment endangering the patient's health.

If a patient wishes to discontinue study treatment at any moment, investigators should explain the importance of remaining on study follow-up, or - failing this - of allowing routine follow-up data to be used for study purposes.

A premature discontinuation of study treatment must be notified by e-mail to the clinical study manager of the CTU as soon as the investigator is aware and reported in the patient CRF. The reasons and date of the discontinuation should be documented in the patient's medical file. Study treatment discontinuation should not lead to patient withdrawal from the study: patients discontinuing their study regimen have to be followed-up according to the scheduled study visits until the end of the study and all data should be collected (under the condition that informed consent has not been withdrawn). They should receive the best possible care given their health status and current best knowledge.

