## 10. LABORATORY EVALUATIONS

### Blood samples collection and tests

Blood samples will be taken:

- (i) at screening phase, to measure HCV RDT and HCV RNA
- (ii) at DAA initiation for positive HCV RNA patients, to measure HBsAg and HIV RDT, complete blood count, serum transaminases, serum creatinine, fasting glycemia, prothrombin time, bilirubin, albumin,
- (iii) at week 4, to measure complete blood count, serum transaminases and serum creatinine,

- (iv) at week 8 and week 12, to measure serum transaminases and serum creatinine,
- (v) at week 24, to measure complete blood count, serum transaminases, serum creatinine, plasma HCV-RNA viral load;

|                                               | test     | DAA       | W4       | W8       | W12       | W24       |
|-----------------------------------------------|----------|-----------|----------|----------|-----------|-----------|
| Complete blood count: EDTA (mL)               |          | 2         | 2        |          |           | 2         |
| Biochemical analysis: Plasma, plain tube (mL) |          | 5         | 5        | 5        | 5         | 5         |
| Coagulation profile: Plasma citrate (mL)      |          | 2         |          |          |           |           |
| Plasma HCV RNA: EDTA tube (mL) or DBS         | 5        |           |          |          |           | 5         |
| Biobank: EDTA (mL)                            |          | 5         |          |          | 5         | 5         |
| Total number of tubes at each visit    | 1 | 4  | 2 | 1 | 2  | 4  |
| Quantity of blood at each visit (mL)   | 5 | 14 | 7 | 5 | 10 | 17 |

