**11.1.5. Adverse event of special interest (AESI)**

AESI will be considered as SAEs and therefore declared as such to the promoter.

For this research, AESI include:

- Any grade 4 biological or clinical event;
- Any event leading to permanent or temporary discontinuation of the investigational medicinal product;
- Any hepatitis B virus (HBV) reactivation
- Cardiac arrhythmias

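### HBsAg-positive patients who complete DAA treatment stop tenofovir at W24, and neither a liver test nor an HBV handover is scheduled after that

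*Protocol*

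**What the plan says.** All references are to the Protocol.

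- **Tenofovir rule** (section 8, Patients with HBV co-infection): "If HBsAg is positive, a treatment by tenofovir will be initiated from inclusion until 12 weeks after discontinuation of HCV treatment".
- **DAA course** (section 8, Treatments used in the study): sofosbuvir and daclatasvir start at the first provincial hospital consultation (W0) and "will be provided to patients for a total duration of 12 weeks".
- **AST/ALT** (section 2 and section 9 schedules): marked at W0, W4, W8, W12 and W24. The W28 cell is empty in both schedules.
- **Blood samples** (section 10): the last draw is "at week 24, to measure complete blood count, serum transaminases, serum creatinine, plasma HCV-RNA viral load". The blood-volume table has no W28 column.
- **W28** (section 9): the only item marked is "Consultation and clinical exam". The visit text adds: "This visit will be the last visit of the study".
- **Handover at W28** (section 9, Visit W28): for patients with cirrhosis, "Recommendations to continue liver ultrasound follow-up every 6 months will be given for cirrhotic patients". Nothing comparable is written for HBsAg-positive patients.
- **Early DAA stop** (section 9, Permanent study treatment discontinuation): "patients discontinuing their study regimen have to be followed-up according to the scheduled study visits until the end of the study".
- **Safety definition** (section 11.1.5): the events of special interest include "Any hepatitis B virus (HBV) reactivation", with no time limit, and are declared as SAEs. Section 11.2 makes adverse events reportable up to the end of each participant's follow-up.

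**The concern.** The study starts tenofovir in HBsAg-positive patients and later stops it. It also names HBV reactivation as an event to be reported like an SAE. One would then expect at least one scheduled liver test after the stop, or a stated transfer to HBV care. For patients who complete treatment as planned, the protocol has neither.

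What is at stake is patient safety and, to a lesser degree, the secondary objective on the safety of the 12-week regimen. A reactivation without symptoms between W24 and W28 would be reportable, but no scheduled test could show it. The patient would then leave the study without a stated HBV follow-up.

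These are details that this document itself fixes: the stop rule, the visit schedule, the blood volumes and the content of W28. A statistical analysis plan would not supply a missing blood test.

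**Working it through.** The protocol gives no figure to reproduce here. The check is schedule arithmetic.

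**Inputs**
- DAA start: W0. Full course: 12 weeks (section 8, Treatments used in the study).
- Tenofovir continues for 12 weeks after the end of DAA (section 8, Patients with HBV co-infection).
- Scheduled AST/ALT: weeks 0, 4, 8, 12, 24 (schedules in sections 2 and 9; section 10).
- Last visit: W28 (section 9, Visit W28).
- HBV DNA: not in any schedule.

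**Step 1: when tenofovir stops.** If DAA ends at week s, tenofovir ends at week s + 12. For a completer, s = 12, so it ends at 12 + 12 = W24.

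**Step 2: what is scheduled afterwards.** No AST/ALT week lies after week 24, so the count is 0. The W24 sample itself is drawn as tenofovir ends and reflects the state on tenofovir.

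**Step 3: length of the window.** 28 − 24 = 4 weeks of follow-up off tenofovir without a scheduled test.

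**Step 4: patients who stop DAA early.** They stay on the scheduled visits, so their W24 AST/ALT falls 24 − (s + 12) = 12 − s weeks after tenofovir ends.

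| DAA ends | Tenofovir ends | W24 AST/ALT falls | Scheduled AST/ALT after the stop |
|---|---|---|---|
| W4 | W16 | 8 weeks after | 1 |
| W8 | W20 | 4 weeks after | 1 |
| W12 (full course) | W24 | 0 weeks after | 0 |

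The gap therefore belongs to completers only.

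**Step 5: does another rule fill the gap?**
- *HBV DNA sentence* (section 8, Patients with HBV co-infection). It calls for HBV DNA when ALT rises suddenly during follow-up of HCV treatment, in order to look for occult HBV, and allows tenofovir to be started. It is most naturally a rule for patients not already on tenofovir. It does not cover HBsAg-positive patients after tenofovir.
- *Aminotransferase monitoring* (section 11.2.2). It asks for monitoring and sends elevated values to the Decision Support Committee. It stands under the DAA risks and adds no test to the schedule.
- *Follow-up of SAEs* (section 11.2). It applies once an event has been recognised and does not help to find one.

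**Step 6: with an AST/ALT added at W28.** A completer would have 1 test, 28 − 24 = 4 weeks after the stop. That is the interval the present schedule already gives a patient who ends DAA at W8.

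**Number of patients.** It cannot be derived. The group is the part of the 300 planned RNA tests (section 14) that is RNA-positive, linked to care, HBsAg-positive and completes DAA. The protocol gives no HBsAg, linkage or completion share for this population.

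**The case against.** The strongest reply accepts the arithmetic and disputes its weight.

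- **The harm is not documented.** No section says that stopping tenofovir carries a risk of reactivation, or when it would show. Listing reactivation as an event of special interest creates a duty to report, not a duty to schedule laboratory surveillance. This stands, and it keeps the point minor. It does not remove the gap, since the protocol itself covers these patients with tenofovir around DAA.
- **Safety nets exist.** These are the W28 clinical exam, adverse event reporting, Decision Support Committee advice on liver events, and unscheduled tests, which nothing forbids. Section 8 leaves drugs other than the study products to the sites' usual procedures, section 3 mentions national hepatitis B and C guidelines, and section 13 announces an operation manual. This stands in part. A flare with symptoms could be caught, and sites may arrange HBV care on their own. But none of these texts schedules a test after W24 or states a handover.
- **The contrast of 0 with 1 test is a by-product of fixed visits.** This stands. It does not show that a lower standard was intended for completers.
- **One test at the last visit is a weak remedy.** This stands in part. It cannot show later flares and leaves no study visit at which to act on the result. The referral is therefore the more important half of the fix.

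A reader might go further and infer that the protocol contains an HBV DNA trigger for these patients that cannot fire because no ALT is measured. The text does not support that. The sentence concerns occult HBV during follow-up of HCV treatment, so no rule is broken; this situation is simply not addressed.

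**Conclusion.** The point holds as a minor safety gap. HBsAg-positive patients who complete 12 weeks of DAA have 0 scheduled liver tests after tenofovir stops, a window of 4 weeks within follow-up, and no stated HBV handover when they leave the study.

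It assumes that DAA starts at W0 and runs for 12 weeks without interruption, and that tenofovir is stopped as the rule says. HIV co-infected patients whose ART contains tenofovir might continue it; the protocol does not address this.

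A reader might also infer that reactivations will be missed in appreciable numbers, that the tenofovir duration is wrong, or that the trial's results are at risk. The protocol supports none of these. It gives no rate or timing of reactivation, the group is small and of unknown size, and neither the primary endpoint nor any endpoint compared between arms depends on it.

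**What to change.** Leave the tenofovir rule as it is and make three small additions.

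1. **Section 9, Visit W28:** HBsAg-positive patients are referred for HBV care at this visit. This also covers the time after the study, which a single test cannot.
2. **Schedules in sections 2 and 9, and the blood table in section 10:** an AST/ALT at W28, footnoted for HBsAg-positive patients. In the blood table this is one plain tube of 5 mL.
3. **Section 8, Patients with HBV co-infection:** in these patients an elevated ALT at W28 leads to HBV DNA and consultation of the Decision Support Committee, in line with section 11.2.2. Give the cut-off, for example a grade on the ANRS scale already used for adverse events. Any rise since W24 would not do as a trigger, because ordinary variation would set it off.

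The cost is one extra tube at an existing visit for a few patients, occasional HBV DNA tests, and a phone call for abnormal results because no visit follows W28.

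The tentative agenda put the last visit in April 2023 and the current version is dated July 2023, so some patients may already have passed W28; the protocol does not say. The referral could still be offered to them.
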